### Data Resources and Variable Construction

The analytic dataset for **Aim 1 **(*internal to the hospital*) will be derived from acute and outpatient DAD hospitalizations linked to the registry data. The dataset will include the following variables: month and year of discharge, CMG, CIHI-defined age group, hospital, region of residence (HA), length of stay (LOS), ICD-10-CA codes, indicator of death, and Adjusted Clinical Groups (a measure of health status [28]). The number of inpatient separations per year, for the conditions to be studied (Table 1), is expected to exceed 5,000. We will analyze hospital separations over the period from fiscal year 2005/2006 through to, and including, 2012/2013, to ensure consistent application of CMG+ across all years.

We will consider the effect of data quality and completeness on the results. The most recent multi-stage randomized studies of DAD data quality, which involve clinical chart re-abstractions, have been conducted by CIHI and have found the majority of data elements in the DAD are accurately reported [35], with comorbidity reporting being an important exception. We will use the results of these studies to exclude those ICD-10-CA codes susceptible to being affected by coding practice changes. Further, we will link Medical Services Plan data to hospital separation data to evaluate completeness of reporting (a means to validate procedure information in the DAD).

One comprehensive analytic dataset will be created for **Aim 2 **(*external to the hospital*) for the years 2005/2006 through 2012/2013. This analytic dataset will be the product of linking acute hospital, registry and continuing care datasets with summarized physician fee-for-service expenditure data. The hospital data will be used to calculate rates of: readmission, admissions from the emergency department and ambulatory care sensitive admissions. The analytic dataset will include admission date, CMG, hospital, region of residence, ICD-10-CA codes, procedure date and whether the patient was admitted from the ED. Readmissions at separate hospitals will be attributed back to the incident hospitalization. The analytic dataset will include an indicator variable to represent incident cases of new home care in the period immediately following discharge from acute care. A variable representing the amount of physician services will be determined from the physician fee-for-service Medical Services Plan (MSP) data linked to patient data.

We recognize that approximately 20% of physicians are not paid by on a fee-for-service basis, so we will limit our inferences to physicians and expenditures paid by fee-for-service as we expect salaried physicians to be less likely to be affected by the incentives of ABF. We will identify those physicians paid primarily by fee-for-service using an information resource being developed at CHSPR for a separate project.

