#### Information Base for Supporting ABF

The success of ABF is critically linked to the ability to measure 'weighted' hospital output accurately. Methods for characterizing hospital output according to the patients' mix of clinical conditions and interventions have become common and are known as case mix adjustments. The most popular method is diagnosis related groups, or DRGs [20], though variants of DRG have been developed, each customized to address local policy and health delivery characteristics and objectives [21,22]. In Canada, all acute inpatient discharge data submitted to the Canadian Institute for Health Information's (CIHI) Discharge Abstract Database (DAD) are case-mix-adjusted using their Case Mix Group (CMG+) methodology [23]. Case mix adjustment is important since it weights hospital discharges according to their expected relative use of resources (and therefore cost). Each CMG+'s expected relative cost is represented by a resource intensity weight (RIW). As the length of stay has no bearing on the RIW value assigned (with minor exceptions for patients with exceptionally long lengths of stay), the incentive is to shorten lengths of stay in order to keep actual costs below the RIW-based case-specific relative amounts.

The veracity of weighting hospital output by RIW is contingent on accurately reported clinical data. CIHI's clinical chart re-abstractions have shown that Canadian hospitals have modified their clinical coding behaviour to maximize RIWs even in the absence of direct financial incentives to do so [18,19]. This behavior introduces an additional challenge to our study and requires us to be able to differentiate actual changes in activity mix as a result of the changing financial incentives from apparent changes in activity mix that are merely shifts in coding practices.

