### Analysis

Initially, we will provide descriptive analyses of the overall trend in provincial LOS and case mix adjusted volume. We will then construct a multivariate zero-truncated Poisson regression model to identify factors associated with length of stay for each condition included in Table 1. The dependent variable, length of stay of patient *i*, is *Y*_*i*_. The regression model effects include: hospital and patient level effects, ***X***_***i***_, (such as age and ACG). Hospital level clustering will be incorporated into the model. The model is:

where time and policy (and interaction between time and policy) represent study month (1,2,3...) and an indicator variable for ABF, respectively.

If the MoHS changes ABF policy during the study period (e.g., to 30% of acute funding), we will change the parameterization of the model to reflect the change. The parameters of interest are θ and τ, where θ represents an immediate change in the length of stay and τ represents a change in the trend in length of stay. The results will be presented as absolute and relative changes to facilitate interpretation. While we are confident these methods are appropriate for the data and the questions being addressed, if small sample sizes inhibit analysis, we will explore composite measures (which combine multiple conditions) for standardized rates [36-38].

We will use a linear regression model to examine the relationship between ABF and hospitals' case mix adjusted volume of cases (transformed for normality if needed). The dependent variable, *Y*_*i*_, is the hospital's monthly number of case mix adjusted cases. Repeated measures (clustering) on hospitals over time will be incorporated into the model through ***X***_***i***_, a vector of hospital effects. The regression equation is written:

where the parameters of interest are change in level (θ) and change in trend (τ). We will construct a regression model for overall weighted cases plus a separate regression model for each condition included in Table 1.

We will model the number of in-hospital medical and surgical deaths, *Y*_*i*_, (as described in Table 2) relative to the total number of separations, *N*_*i*_, using a Poisson model for count data. The vector ***X***_***i ***_will include hospital effects and adjust for repeated measurements on the same hospital. The regression model is written:

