where the parameters of interest are change in level (θ) and change in trend (τ). The vector ***X***_***i ***_will include effects to control for repeated measures on physicians and hospitals plus will adjust for patient level effects, such as age and comorbidity burden (derived from CMG).

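### Volume is tested only as RIW-weighted cases, so a coding change that starts or speeds up with ABF would pass into θ or τ, and the stated safeguards have no stated route to the weight

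*Protocol article*

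**What the plan says.** The section Information Base for Supporting ABF explains that discharge records sent to the national database "are case-mix-adjusted using their Case Mix Group (CMG+) methodology", and that the RIW attached to each group expresses its expected relative cost. It reports that "Canadian hospitals have modified their clinical coding behaviour to maximize RIWs even in the absence of direct financial incentives", and says that this behaviour "requires us to be able to differentiate actual changes in activity mix as a result of the changing financial incentives from apparent changes" that are only coding.

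The Analysis section then defines the volume outcome: the dependent variable "is the hospital's monthly number of case mix adjusted cases". It continues: "We will construct a regression model for overall weighted cases plus a separate regression model for each condition included in Table 1". The parameters of interest are the change in level (θ) and the change in trend (τ). No model of unweighted separations is given, although the Design section mentions the number of discharges among the quantities expected to vary by care type.

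Two safeguards appear under Data Resources and Variable Construction. One rests on chart re-abstraction studies that have been carried out: "We will use the results of these studies to exclude those ICD-10-CA codes susceptible to being affected by coding practice changes". The other links Medical Services Plan data to hospital separations, to judge completeness and validate procedure information. The same paragraph singles out comorbidity as the field that is not reliably reported.

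**The concern.** Weighted volume is the number of separations multiplied by their mean RIW. A model of the product alone cannot tell more patients from heavier weights. Payment by case gives hospitals a reason to code more heavily from April 2010, and the effect runs in the direction of the hypothesis.

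The safeguards do not clearly reach this. A completed re-abstraction study can show which codes have been unreliable; it cannot show which codes will move under a new incentive up to 2012/2013. The article also does not say whether an excluded code is ignored in selecting cases, removes the whole case, or leads to regrouping. Only the last two could alter the weighted total through the RIW. Validating procedures leaves comorbidity coding unchecked.

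At stake is the reading of a positive volume result: policy makers could be told that activity rose when only the recorded severity did.

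**Working it through.** The article gives no sample size, significance level or power for this outcome, so there is no figure to reproduce. The check is of the mechanism.

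**Inputs from the article**
- Study window 2005/2006 to 2012/2013: 8 × 12 = 96 months.
- ABF from April 2010: 5 × 12 = 60 months before, 36 after.
- Segmented model with time, policy and their interaction.

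**Inputs assumed**
- 1,000 weighted cases a month at baseline, with the true number of cases constant throughout.
- Interaction counted from the first ABF month, so that θ is the immediate change.

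**Identity.** V = N × w, with N separations and w mean RIW, so log V = log N + log w. With N fixed, any percentage change in w is the same percentage change in V.

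**Result when only the mean weight changes**

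| Change in mean RIW | θ (cases per month) | τ (cases per month, per month) |
|---|---|---|
| Steady drift of 0.5% to 2% of baseline a year, same rate before and after | 0 | 0 |
| Step at ABF of 1%, 2%, 5% | +10, +20, +50 | 0 |
| Drift faster from ABF by 0.5%, 1%, 2% of baseline a year | 0 | +0.42, +0.83, +1.67 |

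Arithmetic: 1,000 × 0.02 = 20; 1,000 × 0.01 / 12 = 0.83. By the last study month, 35 months after the first ABF month, a 1% a year acceleration has added 35/12 × 1% = 2.9%.

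**Would it be declared significant?** This needs further figures that the article does not give. Assumed: 25 hospitals, independent monthly noise with a coefficient of variation (CV) of 5% or 10%, a two-sided 5% test, and 2,000 simulations.

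| Scenario | Parameter | CV 5% | CV 10% |
|---|---|---|---|
| Steady drift, 1% a year | θ | 4% | 5% |
| Steady drift, 1% a year | τ | 4% | 5% |
| Step of 1% | θ | 64% | 20% |
| Step of 2% | θ | 99% | 64% |
| Acceleration of 0.5% a year | τ | 60% | 21% |
| Acceleration of 1% a year | τ | 99% | 59% |

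These rejection rates are illustrative. Month-to-month correlation or noisier hospitals would lower them, but would not remove the bias in the first table.

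**With the fix.** In every scenario above, unweighted separations and a series weighted independently of later coding give θ = τ = 0 by construction, because true cases do not change.

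**The case against.** Several stronger readings are tempting, and the article does not support them.

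- *Coding alone would confirm Hypothesis 1.1.* It would not. The hypothesis also requires length of stay to fall, and heavier coding leaves the crude stay unchanged. An adjusted stay could shift if a severity covariate were itself inflated by coding, but the article does not say that its health-status measure (ACG) would be affected in that way.
- *Any drift biases the result.* Drift that continues at its earlier rate is absorbed by the time term, and the article says that such coding predates direct incentives. Only a change at ABF does harm.
- *Code exclusion is the only safeguard.* The claims linkage is a second one. Stratification by care type, with separate condition models, would also make some artefacts visible, although the article does not present it as a coding check.
- *The re-abstraction studies all predate ABF.* Those used for the exclusions are undated in the text. It is safe to say only that they are complete.
- *The RIW certainly stays as assigned.* The article is silent. Regrouping or dropping cases is not ruled out, and a fuller plan may specify it.
- *Comorbidity derived from CMG contaminates the volume model.* That adjuster belongs to the physician-expenditure model. Inflated severity there would lower adjusted spending, against Hypothesis 2.3. It is a separate and secondary point.
- *Hospital-month cells are too sparse for a linear model.* This depends on an unstated number of hospitals and on a separations figure given as a floor, and the article offers composite measures as a fallback.

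It is also fair to say that ABF pays for type as well as volume of care, so a genuine move to heavier cases is part of the effect under study. That stands, and the fix has to allow for it. What these objections leave untouched is that the article sets itself a separation task and then models only the product, with no stated route from its safeguards to the weight.

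**Conclusion.** The point holds for the volume half of Hypothesis 1.1. A coding change that starts or accelerates at ABF would by itself produce a positive θ or τ, one for one with the change in mean RIW: +2% for a 2% step. The size of any such change in B.C. is not known from the article; 0.5% to 5% is an assumed range. The conclusion rests on the RIW being the case-mix weight, which the background section indicates and the Analysis wording on weighted cases supports, and on code exclusion not already being carried into the CMG and RIW, which the article leaves unstated. It does not make the volume analysis worthless. It means that a positive result could not be attributed to activity from the planned model alone. The change should be made before the analysis is run.

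**What to change.** Keep the weighted-case model and add the following, with the same segmented terms and hospital effects:

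1. Unweighted separations per hospital-month, in a log-link count model.
2. Mean RIW per separation.
3. A weighted series that uses one fixed set of average weights from before ABF, by principal diagnosis or procedure group and without comorbidity, for all eight years.

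State how an excluded ICD-10-CA code affects case selection, the CMG and the RIW.

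Rule for interpretation: attribute a rise in weighted volume to more activity only to the extent that series 1 or series 3 moves. Report a rise confined to series 2 as not distinguishable from coding change. Series 3 keeps credit for a real shift towards heavier groups.

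Name appendectomy and leg fracture, for which Table 1 expects no response, as a coding-drift check: a rise in their weighted cases or mean RIW at ABF would point to coding. No rise there would not clear conditions with more room for recoding.

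Cost: analysis wording and a few extra model runs on data already held. Limits: fixed weights miss genuine change in severity within a group, and they do not remove recoding of the principal diagnosis itself.

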### Analysis

Initially, we will provide descriptive analyses of the overall trend in provincial LOS and case mix adjusted volume. We will then construct a multivariate zero-truncated Poisson regression model to identify factors associated with length of stay for each condition included in Table 1. The dependent variable, length of stay of patient *i*, is *Y*_*i*_. The regression model effects include: hospital and patient level effects, ***X***_***i***_, (such as age and ACG). Hospital level clustering will be incorporated into the model. The model is:

where time and policy (and interaction between time and policy) represent study month (1,2,3...) and an indicator variable for ABF, respectively.

If the MoHS changes ABF policy during the study period (e.g., to 30% of acute funding), we will change the parameterization of the model to reflect the change. The parameters of interest are θ and τ, where θ represents an immediate change in the length of stay and τ represents a change in the trend in length of stay. The results will be presented as absolute and relative changes to facilitate interpretation. While we are confident these methods are appropriate for the data and the questions being addressed, if small sample sizes inhibit analysis, we will explore composite measures (which combine multiple conditions) for standardized rates [36-38].

We will use a linear regression model to examine the relationship between ABF and hospitals' case mix adjusted volume of cases (transformed for normality if needed). The dependent variable, *Y*_*i*_, is the hospital's monthly number of case mix adjusted cases. Repeated measures (clustering) on hospitals over time will be incorporated into the model through ***X***_***i***_, a vector of hospital effects. The regression equation is written:

where the parameters of interest are change in level (θ) and change in trend (τ). We will construct a regression model for overall weighted cases plus a separate regression model for each condition included in Table 1.

We will model the number of in-hospital medical and surgical deaths, *Y*_*i*_, (as described in Table 2) relative to the total number of separations, *N*_*i*_, using a Poisson model for count data. The vector ***X***_***i ***_will include hospital effects and adjust for repeated measurements on the same hospital. The regression model is written:

The parameters of interest are those associated with immediate change in the number of deaths (relative to the number of discharges, *N*_*i*_) and a change in the trend of number of deaths. We will explore the use of zero-inflated Poisson (ZIP) models if we find an abundance of counts of 0.

Similar to the approaches described above, we will use a linear regression model (suitably transformed for normality) to detect changes in hospital expenditures associated with ABF implementation (including adjustments for effects of inflation) and controlling for repeated measures on hospitals.

Following published methods for calculating hospital readmission rates [31], we will calculate overall readmission rates using a multivariate Poisson model for count data, controlling for repeated measures on hospitals. We will also construct separate models for the conditions listed in Table 3. The regression models of monthly hospital readmission rates will include effects for hospital, time and a binary variable for ABF. The parameters of interest represent immediate change in readmission and change in trend over time.

We will use a linear regression model to examine the relationship between the number of (monthly) new home care patients and ABF. The unit of observation will be the number of new home care patients within an HA and we will control for repeated measures over time. The effects of primary interest are those associated with immediate change in new home care patients and a change in the trend of home care patients. Given stable monthly count data at the HA-level, we expect to be powered able to detect moderate and large sized effects.

Similar to the methods described above, we will model the number of monthly readmissions to acute care from home care using a Poisson model for count data and adjust for HA and hospital effects. The parameters of interest are those associated with immediate change in the number of readmissions to acute care from home care and a change in the trend of number of readmissions.

We will also use a log-transformed model to examine the association between patients' fee-for-service physician expenditures (fee-adjusted) over time, and implementation of ABF. The regression equation for patients' fee-for-service, fee-adjusted, physician expenditures is written:

where the parameters of interest are change in level (θ) and change in trend (τ). The vector ***X***_***i ***_will include effects to control for repeated measures on physicians and hospitals plus will adjust for patient level effects, such as age and comorbidity burden (derived from CMG).

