## Background

Accounting for $46-billion - or 36% of public spending on health care [1] - hospitals are a major target for cost reductions through efficiency initiatives in Canada. Some provinces are considering payment reform as a vehicle to achieve this goal. The use of financial incentives to increase hospital efficiency is now widespread in Europe and has occurred in the United States (US) since 1983 [2-4]; however, the approach remains largely untested in Canada [5].

In April 2010, the British Columbia (B.C.) provincial government implemented activity based funding (ABF) for hospitals, marking a fundamental change to the method of funding acute hospital care. ABF will direct up to 20% of available funds to acute hospitals on the basis of types and volume of services. This change is significant in an industry accustomed to historically-based global budgets and unaccustomed to detailed scrutiny of what services are provided to B.C.'s 4.5 million residents and at what cost.

While this change in hospital funding is being implemented in B.C., a debate over the relative merits of hospital ABF is unfolding across Canada [6,7]. For example, the Canadian Medical Association and the B.C. Medical Association have recently staked positions supportive of ABF [8-10], although support for ABF among the medical community is mixed [11,12]. The Canadian Nurses Association supports an increasing emphasis on output measurement [13] but falls short of endorsing ABF, while other groups are calling for more comprehensive baseline data [14]. Although there has been no formal examination of the effects of ABF policies in Canada - in part because B.C. is the first province to adopt ABF for acute hospitals on a large scale - several other provinces are considering adopting similar funding models.

This project will provide an evidence base on the impacts of ABF, including changes in the type, volume, cost, and quality of services provided. Policy- and decision-makers in B.C. and elsewhere in Canada will be able to use this evidence as a basis for policy adaptations and modifications.

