### Study Limitations

While we are leveraging the natural experiment of a significant change in hospital funding, we are limited in the type of study design we can use. Since the MoHS' ABF initiative includes all hospitals, it is not possible to 'randomize' hospitals to ABF and non-ABF groups as to isolate the effect of the implementation of ABF. We are not including another province's hospitals to act as a 'control' group due to the potential confounding from reporting differences between provinces, hospital funding policy changes in other provinces and the potentially insurmountable problems associated with, but undoubtedly lengthy time required to, securing data access in multiple provinces. Given these constraints, a longitudinal design is the strongest possible design. Our study will be limited to administrative datasets, precluding the use of detailed clinical data that might inform our analyses.

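### All hospitals switch to ABF in the same month, but no model has a month-level error, so confidence intervals for θ and τ are too narrow whenever hospitals share month-to-month variation

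*Protocol article*

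**What the plan says.** The Background gives one start date: "In April 2010, the British Columbia (B.C.) provincial government implemented activity based funding (ABF) for hospitals". Study Limitations confirms that the "ABF initiative includes all hospitals" and adds: "We are not including another province's hospitals to act as a 'control' group". Data Resources and Variable Construction sets the window as "the period from fiscal year 2005/2006 through to, and including, 2012/2013".

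The Analysis section describes the time and policy terms as study month, an ABF indicator and their interaction, and names θ and τ as the parameters of interest. It then states how dependence is handled, model by model:

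- Length of stay: "Hospital level clustering will be incorporated into the model".
- Case-mix-adjusted volume: repeated measures enter through a vector of hospital effects.
- Deaths: the covariate vector will "include hospital effects and adjust for repeated measurements on the same hospital".
- Hospital expenditures and readmissions: control for repeated measures on hospitals.
- New home care patients: HA-months, with control for repeated measures over time.
- Readmissions from home care: HA and hospital effects.
- Physician payments: the vector will "include effects to control for repeated measures on physicians and hospitals plus will adjust for patient level effects".

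None of these descriptions includes a month-level error or correlation between hospitals in the same month.

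**The concern.** In any month, every hospital has the same value of time, policy and their interaction. A hospital therefore adds no independent information on what else happened in the province that month. An infection wave or province-wide bed pressure moves many hospitals together and moves the estimated θ and τ with them.

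Hospital clustering judges precision by how much hospitals differ from one another. A disturbance that moves them all alike creates no such difference, so it drops out of the standard error but remains in the estimate. Adding hospitals or patients shrinks the reported error without shrinking the shared part. Modelling serial correlation within each hospital does not help, because the dependence lies between hospitals.

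The study intends to give policy recommendations on cost, mortality and readmission, and it has no control series that could expose a false signal. If shared variation is material, ordinary monthly movement could be read as an ABF benefit or harm.

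**Working it through.** **Inputs from the article.** One switch date, all hospitals exposed, no control. Eight fiscal years × 12 = 96 months; with fiscal years starting in April (an assumption), 5 × 12 = 60 before and 3 × 12 = 36 after. The article gives no hospital count, variance, alpha or power, so there is no figure to reproduce.

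**Assumed inputs.** J hospitals in a balanced panel, independent hospital-month noise with SD σ, a shock with SD δ common to all hospitals in a month, and θ read as the level change at the switch. A linear model stands in for all the models.

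**Formulas (independent monthly shocks).**

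- Hospital-clustered SE of θ = c·σ/√J
- True SD of θ = c·√(σ²/J + δ²)
- Ratio = √(1 + Jδ²/σ²), or √(1 + Jρ/(1−ρ)) with ρ the shared fraction of residual variance
- Actual error of a nominal 5% test ≈ 2[1 − Φ(1.96/ratio)]

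For 60 and 36 months with separate lines, c² = [1/60 + 29.5²/17,995] + [1/36 + 18.5²/3,885] = 0.0650 + 0.1159 = 0.1809, so c = 0.425.

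**One worked case.** J = 60, σ = 15%, δ = 3%:

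- Reported SE = 0.425 × 0.15/√60 = 0.8%
- True SD = 0.425 × √(0.000375 + 0.0009) = 1.5%
- Ratio = √(1 + 60 × 0.0009/0.0225) = √3.4 = 1.84
- Error ≈ 29%; simulations of this case gave 27% to 30%, against about 5% when province-month means were analysed.

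**How it varies with outcome density (J = 60).** The article expects more than 5,000 separations a year for the Table 1 conditions. At that floor, read as per condition, 5,000/12/60 = 6.9 cases per hospital-month and Poisson noise is 1/√6.9 = 38%. Read as a total over eight conditions, it is 0.87 cases and 107%.

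| Shared shock δ | Error, σ = 15% | Error, σ = 38% | Error, σ = 107% |
|---|---|---|---|
| 1% | 8% | 5.5% | about 5% |
| 2% | 17% | 7% | between 5% and 6.5% |
| 3% | 29% | 9% | between 5% and 6.5% |
| 5% | 48% | 17% | 6.5% |

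**Effect of autocorrelated shocks.** Simulation, 2,000 runs per cell, true θ = τ = 0; ratio of true SD to hospital-clustered SE for θ, and error rate:

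| J, ρ | Independent shocks | AR(1) 0.5 shocks |
|---|---|---|
| 20, 1% | 1.11, 8% | 1.25, 11% |
| 50, 5% | 1.91, 30% | 2.85, 48% |
| 80, 10% | 3.16, 54% | 4.93, 68% |

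With ρ = 0 the ratio is 1.0 and the error about 5%. Results for τ are nearly the same. Hospital fixed effects with model-based errors do no better (J = 50, ρ = 5%, independent shocks: ratio 1.87, 29%). With five HA-level units (assumed) and ρ from 5% to 30%, the ratio is 1.11 to 1.83 and the error 7% to 19%.

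**Checking remedies.** Ordinary least squares on month means gives about 5% when shocks are independent, but 8% to 23% with AR(1) 0.5 shocks. Two-way clustering by hospital and month, with 60 hospitals and AR(1) 0.5 shocks, gives 17%, 21% and 25% at shocks of 2%, 3% and 5%. The AR(1) month effect, AR(1) GLS and Newey-West options were not simulated.

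**The case against.** Much of the case on the other side concerns scope and size, and most of that stands.

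- **Every magnitude is assumed.** A reader might infer that θ and τ are certain to look far more precise than they are, or that false ABF effects would be declared. The article does not support that: with no shared shock, hospital clustering is correct, and with sparse outcomes the inflation is small.
- **The dependence is not handled by hospital alone in every model.** Physician payments add physicians, and the home care models use HA terms. Neither adds a month component, so the gap remains.
- **The cancellation is exact only for balanced panels and equal hospital responses.** If hospitals respond unequally, part of the shock survives in the clustered variance. Hence it is largely, not wholly, left out.
- **Some shared variation is predictable or adjusted for.** Holidays and much of the infection season are seasonal mean effects, and the article plans to remove price inflation and fee changes. Unmeasured shared variation is still uncovered.
- **Patient-level models may not be hit hardest.** No truncated-Poisson or patient-level model was simulated, so no such ranking is claimed.

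It can also be said that the equations are not visible and that a condensed article leaves variance details to an analysis plan. This carries less weight: the text states its dependence structure model by model and declares the methods suitable. Following it as written leaves the shared component out.

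**Conclusion.** The point holds as a defect of the stated analysis. With one switch date, all hospitals exposed and no control, θ and τ rest on 96 months, and the named hospital, physician and HA terms do not carry month-to-month variation shared across hospitals. Standard errors are too small whenever such variation exists.

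How much too small cannot be settled from the article. Over the assumed hospital-level range (20 to 80 hospitals, 1% to 10% of residual variance shared), they fall short by a factor of about 1.1 to 5. Sparse condition-specific models may be close to nominal; overall volume and other high-volume aggregates are the most exposed. These figures rest on balanced linear panels and the assumed hospital counts and variances.

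**What to change.** In all the regression models of the Analysis section, add a random effect for each of the 96 study months (not the 12 calendar months), shared by all hospitals and with AR(1) correlation across months. Alternatively, estimate θ and τ from risk-adjusted province-month means, using AR(1) GLS or Newey-West errors with a small-sample correction, at least as the basis for inference on aggregate outcomes. Do not rely on two-way clustering by hospital and month alone: it omits dependence between different hospitals in adjacent months. State that the effective sample for the policy contrast is 96 months, 60 before and 36 after if fiscal years start in April.

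No new data are needed. The cost is wider confidence intervals and some extra modelling work, more so for month effects with AR(1) correlation in the zero-truncated Poisson models than for the province-month analysis.
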